### **Sample Size Calculation**

The sample size is calculated using G\*Power 3.1. To elucidate the differences in the executive function tests with a statistical power of 0.9, a conservative effect size of 0.65 based on a previous systematic review with the average effect size calculated regarding the effect of exercise on executive function in children with ADHD [24], a two-tailed alpha level of 0.05, it is determined that 10 participants per group will provide adequate power to detect statistically significant differences. Assuming a 30% loss in the intervention, we will need to approach about 42 eligible participants to achieve the planned sample.

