## **Outcomes Measurements**

Before (T0) and after (T1) the 12-week intervention period, as well as another 12-week follow up (T2), several different indicators will be recorded, including executive function, cerebral hemodynamic response, weekly PA levels, physical fitness, feeling state, and enjoyment and adherence to the intervention. All assessments will be conducted by trained research staff blinded to group allocation. To ensure the accuracy and consistency of the measurements, a measurement training session and protocol manual, including specific instructions for

conducting all assessments, will be provided to the research staff. A senior researcher will be present during all the testing sessions. All physical assessments will be conducted in a sensitive manner (e.g., weight/waist circumference will be measured in a private setting), and the cognitive function tests and questionnaires will be completed under exam-like conditions. Also, participants will be instructed to follow similar diets on the main trial days. Only distilled water will be allowed before the tests in the main trials.

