## **Primary Outcome**

### **Executive Function**

Executive function will be assessed using a battery of tests on a laptop computer that will take approximately five minutes to complete. The battery of tests include the Colour-Word Stroop Test (CWST) and Eriksen Flanker Test (EFT) which are classic tasks that measure inhibition response, one of important components of executive function. Previous studies have reported medium to large effect size of the different exercise intervention programs on inhibition of children and adolescents with ADHD [27, 28, 40]. In these two tests, both reaction time and response accuracy will be recorded and analyzed. This battery has been used previously by research group members to investigate the effect of exercise on cognition in young people [59]. The instructions for each test will be provided to the participants and they will be allowed to ask questions for clarification. Participants will be familiarized with the testing battery seven days prior to the main trial, and each test will start with 3-6 practice stimuli to re-familiarize participants with the task at hand and eliminate any potential learning effects. In the main trial, participants will complete the tests in a group of 3-4 participants. They must remain silent from the other participants so that they cannot interact with others while taking the tests.

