### **Statistical analyses**

Statistical analyses of the primary and secondary outcomes will be conducted with the IBM SPSS Statistic for Windows, Version 20.0 (2010 SPSS Inc., IBM Company Armonk, NY). Intervention effects for the primary and secondary outcomes will be examined by two-way (trial × time) analysis covariance (ANCOVA), including group as a fixed factor, pre-post intervention difference (change) as the dependent variable, and age, attendance, sports skill, and ADHD symptoms as covariates. Effect sizes (ES) will be presented as partial eta squared values ( $\eta^2$ ). Pairwise comparison will be performed (post-hoc) with Bonferroni correction, with ES presented as Cohen's *d*. Correlational analysis will also be conducted to evaluate the relationship between the changes in executive function and the fNIRS measures. All data will be presented as mean ± SD, and significance will be set as  $p < 0.05$  for all data analysis.

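### The protocol labels a single change score a two-way trial-by-time ANCOVA and leaves the outcome's own baseline out of the covariates: this costs precision, without bias on average, and leaves the role of T2 undefined

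*Protocol*

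**What the plan says.** One sentence in the protocol, under Statistical analyses, governs all outcomes. It opens "Intervention effects for the primary and secondary outcomes will be examined by" and names the method: effects "will be examined by two-way (trial × time) analysis covariance (ANCOVA"). It then gives the model, "including group as a fixed factor, pre-post intervention difference (change) as the dependent variable", and closes with the covariates: "age, attendance, sports skill, and ADHD symptoms as covariates".

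Under Executive Function, the primary outcome is the Stroop and Flanker tests: "In these two tests, both reaction time and response accuracy will be recorded and analyzed". Under Outcomes Measurements, executive function is among the indicators recorded "Before (T0) and after (T1) the 12-week intervention period, as well as another 12-week follow up (T2"). A T0 value of every primary measure will therefore exist. No other part of the protocol adds it to the model. Under Study Design, controls receive one of the two programmes, by preference, after the first 12 weeks, so they have been offered an intervention by T2.

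**The concern.** There are two separate problems in the one sentence.

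- **Label and model do not match.** A trial-by-time analysis needs repeated values per child. A pre-post difference is a single value, and group is the only fixed factor named. The reader cannot tell whether T2 is meant to enter. If it did, the test would combine the randomised contrast at T1 with a period in which controls are also treated.
- **The baseline of the outcome is missing.** An unadjusted change score fixes the coefficient of the T0 value at 1. Unless the true slope is 1, the residual variance is larger than it need be, and a chance difference between arms at T0 carries into the estimate. With about 10 evaluable children per arm, the trial has little precision to spare.

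The dependent variable and the covariates are written into the protocol itself, so this is not a detail merely left to a statistical analysis plan.

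**Working it through.** **The plan's own figure.** Sample Size Calculation gives 10 per group "with a statistical power of 0.9", using "a conservative effect size of 0.65 based on a previous systematic review" and two-tailed alpha 0.05. This does not follow from the stated inputs alone:

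- Two groups with a standardised difference of 0.65 need 2 × (1.960 + 1.282)² / 0.65² = 49.7, so 50 per arm.
- A one-way three-group ANOVA with f = 0.65 needs 36 in total; 30 gives power 0.86.
- Only repeated-measures set-ups with a correlation the protocol does not state come to about 30.
- The dropout step is close: 30 / 0.7 = 42.9, against about 42.

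The sample size is a separate matter, and nothing below depends on it except the use of 10 per arm and 0.65 for illustration.

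**Label.** With T0 and T1 only, the three-arm group × time interaction has (3−1)(2−1) = 2 numerator degrees of freedom and is the same test as the group effect on change. On simulated data with 10 per arm both gave F = 1.276. With T0, T1 and T2 the interaction has (3−1)(3−1) = 4 numerator degrees of freedom and tests a different hypothesis.

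**Precision.** Assume equal SDs at T0 and T1, scaled to 1, and T0–T1 correlation rho.

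- Change score without baseline: residual variance 2(1−rho).
- With the T0 value as covariate: 1−rho².
- Ratio: (1−rho²) / [2(1−rho)] = (1+rho)/2.

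For illustration, read 0.65 as a difference in raw-score SD units. The n per arm for 90% power is then 49.7 × residual variance, rounded up. Power at 10 per arm uses the noncentral t with noncentrality 0.65 / √(variance × 2/10), unadjusted two-sided alpha 0.05, and residual degrees of freedom 30 − 3 − 4 = 23 without baseline and 22 with it. At rho 0.5 the noncentrality is 0.65/√0.20 = 1.45 without baseline and 0.65/√0.15 = 1.68 with it.

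| rho (assumed) | Change | With T0 | Ratio | n per arm, 90% power | Power at 10 per arm |
|---|---|---|---|---|---|
| 0.3 | 1.40 | 0.91 | 0.65 | 70 → 46 | 0.22 → 0.31 |
| 0.5 | 1.00 | 0.75 | 0.75 | 50 → 38 | 0.29 → 0.36 |
| 0.7 | 0.60 | 0.51 | 0.85 | 30 → 26 | 0.44 → 0.50 |
| 0.9 | 0.20 | 0.19 | 0.95 | 10 → 10 | 0.875 → 0.89 |

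These powers allow for the lost degree of freedom but not for chance imbalance in the added covariate. That takes back a little more and leaves almost nothing at rho 0.9.

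**Choice of dependent variable.** With the T0 value in the model, the same simulated data gave identical group estimates (0.258 and 0.298) whether the dependent variable was change or the T1 value. Only the baseline coefficient differed, by exactly 1 (−0.590 against 0.410).

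**The case against.** The strongest defence is that the change-score analysis is valid. Allocation is randomised, so the estimate is unbiased on average, the test keeps its type I error, and chance imbalance is already in its standard error. That stands. Three stronger readings therefore go too far.

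- *Regression to the mean biases the result.* A reader might infer this from the missing baseline. It does not follow under randomisation. At 10 per arm the SD of a chance baseline difference is √(2/10) = 0.447, which at rho 0.5 moves the change-score contrast by 0.5 × 0.447 = 0.22 SD. This is not a further harm: 0.22² = 0.05 is exactly the variance difference (1.00 − 0.75) × 2/10 already counted above. Setting it against 0.65 would also assume a metric that the protocol does not state. And √(2/10) ignores the stratification by gender, IQ and medication, and the adjustment for age and ADHD symptoms, which reduce imbalance so far as they relate to test performance.
- *The two descriptions give different p-values.* For T0 and T1 they are the same test, also with covariates if these are crossed with time. They part only if T2 enters or the covariates are handled differently.
- *The change score and the other covariates must be replaced.* Once the T0 value is included, change and T1 give the same group estimate. Whether attendance, sports skill and ADHD symptoms belong in the model is a different question that this point does not settle.

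It can also be said that ADHD symptoms, if taken at T0, already act as a baseline. That may be so for the symptom scale, but not for Stroop or Flanker reaction time and accuracy.

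**Conclusion.** The point holds as one of precision and clarity, not of validity. The sentence is internally inconsistent, and its explicit covariate list omits a baseline that will be available for the primary tests. Adding it would cut residual variance by 35%, 25%, 15% or 5% at assumed correlations of 0.3, 0.5, 0.7 or 0.9, with a gain close to nil at the top of that range. These figures rest on equal SDs at T0 and T1 and on a rho that the protocol does not give; the power and sample-size figures also rest on reading 0.65 in raw-score SD units. The label does no harm for T0–T1 alone. It leaves the test undefined if T2 is included. The wording should be settled before outcome data are seen.

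**What to change.** Make two changes to the sentence under Statistical analyses.

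1. For each outcome measured at T0, add its T0 value as a covariate in the group comparison at T1. The dependent variable may be the T1 value or the change. Restrict this to outcomes that have a T0 value: adherence (attendance and dropout) and heart rate during sessions have none.
2. Delete the two-way trial-by-time label, or define it by stating which time points enter. If T2 is analysed, describe that analysis separately and say how the controls' later intervention is treated.

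The cost is one degree of freedom for the baseline covariate (23 to 22 residual degrees of freedom with 30 children and the four listed covariates), using data already planned. Adding randomisation factors or removing listed covariates would be a separate decision with its own cost in degrees of freedom.

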Therefore, the primary aim of the proposed study is to investigate the effect of two different kinds of exercise programs, i.e., a 12-week game-based HIIT (GameHIIT) program and a 12-week game-based structured aerobic exercise (GameSAE) program, on the executive function of children with ADHD. The secondary aim is to explore a possible mechanism behind the potential association between exercise intervention and improvements in executive function. The hypothesis of the proposed study is that both GameHIIT and GameSAE programs will significantly improve the executive function of children with ADHD, compared with those in the control group. A secondary hypothesis is that the GameHIIT group may confer additional benefits when compared with the GameSAE group.

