### **Study Design**

A three-arm school-based randomized controlled trial (RCT) will be conducted to evaluate the effects of two different kinds of 12-week training programs on the executive function of children with ADHD. The design, conduct, and reporting for the RCT adheres to the guidelines of the Consolidated Standards of Reporting trials (<http://www.consort-statement.org/>) [54]. Participants will be randomly assigned to the GameHIIT group, the GameSAE group, or a non-treatment control group using a random number-producing algorithm (with a 1:1:1 allocation ratio within each school). A stratified random sampling procedure will be conducted that considers gender, IQ, and medication status. Raven's Standard Progressive Matrices (SPM) will be used to measure general intelligence. Equal numbers of boys and girls with similar general intelligence will be included in the three groups. Children taking medication will be equally distributed to the three groups. Participants will not be blinded to treatment allocation because of the intervention nature. To avoid contamination between treatment groups, intervention deliverers will be provided with a list of students in the intervention program. Only those on the list can participate in the intervention. During the 12-week intervention period, participants in the control group will maintain their regular PA levels. For ethical reasons, a cross-over study design will be adopted. That is, participants in the control group will receive either GameHIIT intervention or GameSAE intervention according to their preference after a 12-week formal intervention period. Accordingly, participants in the other two groups will have another 12-week follow up. Therefore, it is expected that all participants in the three groups will benefit from the proposed study. The flow diagram of the study design is shown in **Figure 1**.

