### **Enjoyment and Adherence**

Enjoyment will be assessed by the Physical Activity Enjoyment Scale, which is a valid and reliable tool for evaluating perceived enjoyment [65]. Adherence to the intervention program will be evaluated by attendance frequency and dropout rate.

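### The only model for the primary outcome adjusts for programme attendance, which arises after randomisation and has no value in the control arm during the comparison period

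*Protocol*

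**What the plan says.** Under Statistical analyses, the protocol states: "Intervention effects for the primary and secondary outcomes will be examined by two-way (trial × time) analysis covariance (ANCOVA), including group as a fixed factor". The same sentence continues with "pre-post intervention difference (change) as the dependent variable, and age, attendance, sports skill, and ADHD symptoms as covariates". No between-arm model without attendance is named.

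Attendance is given a meaning in one place only, Enjoyment and Adherence: "Adherence to the intervention program will be evaluated by attendance frequency and dropout rate".

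Study Design allocates children to "the GameHIIT group, the GameSAE group, or a non-treatment control group". It restricts access to the sessions ("Only those on the list can participate in the intervention") and says of the comparator: "During the 12-week intervention period, participants in the control group will maintain their regular PA levels". Controls are offered a programme only after the 12 weeks, outside the pre-post interval.

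The primary hypothesis, at the end of the Background, is that "both GameHIIT and GameSAE programs will significantly improve the executive function of children with ADHD, compared with those in the control group".

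**The concern.** A covariate in a randomised comparison should be fixed before allocation. Attendance is produced by allocation and is the means by which the treatment is delivered. Adjusting for it asks how the arms would differ if all children had attended equally. No child in the control arm can supply information on that, because controls have no sessions to attend.

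At stake is the contrast in the primary hypothesis, each programme against control. Depending on how control attendance is coded, the model loses the control arm, or returns a coefficient with a different meaning, far less precision, and exposure to confounding by whatever makes children attend (motivation, symptom severity, family support). Randomisation protects the unadjusted contrast from that confounding; this covariate lets it back in.

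GameHIIT versus GameSAE can still be estimated, but any difference that arises because one programme is better attended is adjusted away.

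**Working it through.** **The plan's own figures.** The protocol attaches no number to attendance, so there is no attendance figure to reproduce. Sample Size Calculation gives an effect size of 0.65, power 0.9, "a two-tailed alpha level of 0.05", 10 per group, and about 42 children after 30% loss. The last step agrees approximately (30/0.7 = 42.9; 42/3 = 14 per arm). The stated power was not reproduced: with 0.65 read as a standardised mean difference, a two-group t-test with 10 per arm has power 0.28. That is a separate matter. Here 0.65, 10 and 14 serve only as inputs.

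**Assumptions.** Change has SD 1. Mean attendance in the exercise arms is 0.80, SD 0.15 (range 0.10 to 0.25). Age, sports skill and ADHD symptoms are left out.

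**Case (a): control attendance blank.** Every control has a missing covariate. A complete-case fit removes all of them, and no contrast with control can be estimated.

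**Case (b): control attendance coded 0.** The model is change = α + β₁·GameHIIT + β₂·GameSAE + γ·attendance + error. Attendance does not vary among controls, so γ is estimated only within the exercise arms, and

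β̂₁ = (mean change GameHIIT − mean change control) − γ̂ × (mean attendance GameHIIT − 0).

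*Precision.* Var(β̂₁) = 2/n + (mean attendance)² / [2(n − 1) × SD²]. With n = 10:
- first term: 2/10 = 0.20
- added term: 0.8² / (18 × 0.15²) = 0.64/0.405 = 1.58
- ratio: (0.20 + 1.58)/0.20 = 8.9, so the standard error is about 3 times larger.

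*Meaning.* If the benefit is proportional to attendance, γ carries all of it and β₁ is 0, although the effect of assignment is 0.65 SD.

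*Bias when exercise does nothing.* If attendance and change correlate at r = 0.3 within arms for other reasons, γ is about 0.3/0.15 = 2 SD per unit of attendance. The bias in β₁ is then about −2 × 0.8 = −1.6 SD, with the opposite sign if r = −0.3.

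**Simulation of case (b)**, 8,000 trials per scenario, attendance clipped to 0–1, one exercise arm versus control, two-sided 0.05 without multiplicity correction. Brackets give the range over attendance SDs of 10 to 25 points.

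| Quantity | Attendance left out | Attendance in |
|---|---|---|
| Standard error, 10 per arm | 0.44 | 1.47 (1.02–2.03) |
| Power, effect 0.65 SD, 10 per arm | 29% | 7% (6–10%) |
| Mean coefficient, benefit proportional to attendance | about 0.65 | about 0 (rejected in 5%) |
| Size of bias, no effect, r = ±0.3 | about 0 | about 1.7 SD (1.1–2.4) |
| False positives, no effect, r = ±0.3, 10 per arm | about 5% | 21% (19–23%) |
| Same, 14 per arm | about 5% | 30% (25–31%) |

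**Second calculation under other assumptions.** Attendance mean/SD was 0.80/0.15, 0.70/0.25 and 0.85/0.08, with 10 or 14 per arm and 3,000 runs per scenario. Attendance multiplied the variance of the contrast by about 3.5 to 35. With benefit proportional to attendance, the adjusted estimate averaged −0.01 to 0.03 and was rejected in 4–5% of runs, against 29–39% without attendance. With no effect and an unmeasured trait driving attendance (loading 0.6) and improvement (loading 0.4), the adjusted estimate was about −0.7 to −2.6 SD, with 13–22% false positives.

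**The case against.** The strongest objections are these.

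- *The model can still be fitted.* This is true under zero coding when attendance varies. The fault is then a wrong estimand, bias and lost precision rather than non-estimability. The protocol does not say how controls are coded, but neither natural coding gives the effect of assignment.
- *The Bonferroni correction is ignored.* The protocol plans it for pairwise comparisons, and the table above is uncorrected. At 0.05/3 (three comparisons assumed), false positives with r = 0.3 are about 9–12% at 10 per arm and 12–19% at 14 per arm, against about 2% without attendance. Power at 10 per arm is about 2–4% with attendance and 16% without. The percentages fall, but the relative inflation does not.
- *The sizes are assumed.* This stands. The protocol gives no attendance mean, spread, correlation with change or control coding, and the variance inflation is sensitive to them. A coefficient of exactly zero needs benefit strictly proportional to attendance. A false benefit needs better attenders to improve less, for which the protocol gives no reason; the opposite sign hides or reverses a benefit.
- *The SAP may settle it.* An SAP may supply what a protocol leaves open. Here the protocol positively names the covariate and offers no alternative model, and no section gives attendance another meaning, such as school attendance.

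**Conclusion.** The concern holds. As written, the only planned model for the primary outcome cannot validly test either programme against control: it excludes the controls, or it conditions on a post-randomisation variable almost collinear with arm. This structural conclusion follows from the text alone.

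Its size rests on the stated assumptions. In the central case with 10 per arm, the standard error is more than three times larger (1.47/0.44 = 3.3), power is cut to about a quarter (7/29), and moderate confounding of attendance with change raises the false-positive rate about fourfold (21% against 5%). This must be corrected before the data are analysed.

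**What to change.** In Statistical analyses, delete attendance from the covariate list of every between-arm model, for primary and secondary outcomes. Compare the arms as allocated, and state that the remaining covariates are values taken before randomisation; the section does not currently say when sports skill and ADHD symptoms are measured.

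If a dose-response question is of interest, describe it separately as exploratory, within the two exercise arms only, with programme as a factor and no causal claim against control. Attendance stays as a descriptive adherence measure, as already planned.

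The cost is one wording change, carried into the SAP if there is one. No new data, participants or visits are needed.

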Recently high-intensity interval training (HIIT) has emerged as a feasible and efficacious strategy for improving the physical health of young people [41-42]. The HIIT can be completed in a short period of time, while resulting in equivalent physiological adaptations to longer sessions of traditional aerobic training [43]. Recent research has suggested that traditional HIIT intervention programs, including running and cycling, may improve executive function in healthy children and adolescents [44-46]. It has been suggested that a very brief HIIT intervention over two weeks reduced off-task behavior and enhanced selective attention in primary school children [44-45]. For children with ADHD, to the best of our knowledge, only one recent study [47] was conducted to investigate the effect of a traditional HIIT program on physical fitness, motor skills, social behavior, and quality of life. In this randomized controlled trial, 28 boys with ADHD were assigned to either a traditional HIIT group or a standard multimodal therapy (TRAD) group. After the three-week intervention, the authors reported that HIIT was more effective in improving motor skills, self-esteem, relations with friends, competence, and subjective ratings of attention, compared with TRAD. However, despite this encouraging preliminary evidence, it remains unclear whether HIIT can be adopted to treat children with ADHD to improve their executive function, a key aspect in many facets of life.

While the limited findings regarding the effects of HIIT on executive function are encouraging, and HIIT has emerged as an enjoyable and effective exercise for children [42], previous studies have tended to prescribe HIIT interventions with a focus on running and jumping [44-46]. The effect of game-based HIIT interventions on the executive function of children have yet to be

investigated. Research of this nature is needed, particularly to determine whether game-based HIIT can improve outcomes (e.g., executive function, social behavior, sports skills, etc.) for children with ADHD.

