### **Social Behavior, Quality of Life, and overall ADHD symptoms**

Conners' Teacher Rating Scale 15-Item (CTRS-15) [61] will be used to measure the social behaviors of participants. It has been widely used to assess problematic behaviors in children with ADHD. Parents will be required to complete a 50-item Child Health Questionnaire-Parent Version (CHQ-PF50) [62] to assess the quality of life of participants. Overall ADHD symptoms will be assessed by the Attention-Deficit/Hyperactivity-symptoms and Normal-

behaviors (SWAN) rating scale [67].

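### The outcome model adjusts for attendance, a post-randomisation measure that controls cannot have, so it no longer estimates the randomised effect against control

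*Protocol*

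**What the plan says.** - **Model.** Under Statistical analyses, a single two-way ANCOVA serves every primary and secondary outcome. Its structure is given as "including group as a fixed factor, pre-post intervention difference (change) as the dependent variable". Four adjustment variables are then listed: "and age, attendance, sports skill, and ADHD symptoms as covariates". No other model for intervention effects is given, and none without attendance.
- **Attendance.** Under Enjoyment and Adherence: "Adherence to the intervention program will be evaluated by attendance frequency and dropout rate". It is therefore attendance at the assigned programme, counted after randomisation.
- **Control arm.** Study Design sets up the arms: "Participants will be randomly assigned to the GameHIIT group, the GameSAE group, or a non-treatment control group". On what controls do in the comparison period, the same section says: "During the 12-week intervention period, participants in the control group will maintain their regular PA levels". Controls are offered a programme only after those 12 weeks.
- **Main hypothesis.** The end of the Background section states it as each exercise programme against control. GameHIIT against GameSAE is the secondary hypothesis.
- **Other covariates.** Nothing under Outcomes Measurements or the outcome headings after it measures sports skill. The Background mentions it when asking "whether game-based HIIT can improve outcomes (e.g., executive function, social behavior, sports skills, etc". ADHD symptoms are listed as a secondary outcome ("Overall ADHD symptoms will be assessed by the" SWAN scale).

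**The concern.** A covariate in a randomised comparison should be fixed before allocation. Attendance is not: it is a consequence of allocation, and in the exercise arms it is the dose of treatment received. Adjusting for it asks how the arms would differ at equal attendance. Exercise children and controls never have equal attendance.

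The comparison most exposed is the main one, exercise against control on executive function, because a whole arm has no value for the covariate. The secondary comparison is affected less. Both exercise arms have attendance, but the assigned programme can influence it, so adjustment no longer compares those groups as randomised.

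Two other covariates add to the problem. Sports skill cannot be entered because nothing measures it, and if it were measured after T0 it could itself respond to training. ADHD symptoms are an outcome of the trial, and the covariate is not tied to T0. If the T1 score were used, the model would adjust away part of the effect.

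**Working it through.** The protocol gives no figure on this point, so there is none to reproduce.

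**Inputs from the protocol.** Three arms at 1:1:1; 10 evaluable children per group; effect size 0.65, read here as a standardised mean difference (the protocol does not name the index); two-sided alpha 0.05.

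**Assumptions.** The protocol gives no attendance figures. The central case is a mean of 80% of sessions with SD 15%, capped at 100%. The range runs from 90% (SD 10%) to 60% (SD 30%). The residual SD is 1.

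**Case 1: controls have attendance missing.** A complete-case ANCOVA needs every covariate, so it deletes all controls. The contrast with control cannot be estimated.

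**Case 2: controls are coded zero.** With ā the mean attendance in an exercise arm and b the within-arm slope of outcome on attendance:

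adjusted effect = unadjusted effect − b × (ā − 0)

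- *Benefit proportional to attendance.* b = 0.65/0.80 = 0.8125, so the adjusted effect is 0.65 − 0.8125 × 0.80 = 0.
- *Benefit unrelated to attendance.* b = 0, so the expected estimate stays at 0.65 but its variance grows:

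variance = σ² × [1/10 + 1/10 + ā²/SSW]

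SSW is the within-arm sum of squares of attendance. Controls contribute nothing to it, so SSW = 2 × 9 × 0.15² = 0.405. The variance is 0.2 + 0.64/0.405 = 1.78σ² and the SE is √1.78 = 1.33, against √0.2 = 0.45 without attendance. Simulation gives about 1.47. It is larger because capping at 100% narrows the spread of attendance and because SSW varies from trial to trial.

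**Simulation, arm indicators only (central case):**

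| Model | Estimate | SE | Power |
|---|---|---|---|
| Without attendance | 0.65 | 0.44 | 29% |
| With attendance, benefit proportional | about 0 | about 1.5 | 5% (alpha) |
| With attendance, benefit unrelated | about 0.65 | 1.47 | 8% |

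Holding mean attendance at 80%, an attendance SD of 10% gives an SE of about 2.0, and an SD of 20% gives about 1.2.

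**Simulation with three baseline covariates added (10 per arm, 3,000 trials per row).** Without attendance, the estimate is 0.63 to 0.65, the SE about 0.47 and power 24% to 27% in every row. With attendance:

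| Attendance mean / SD | Estimate if proportional | Estimate if unrelated | SE | Power if unrelated |
|---|---|---|---|---|
| 90% / 10% | 0.04 | 0.63 | 2.69 | 5% |
| 80% / 15% | 0.00 | 0.63 | 1.55 | 7% |
| 70% / 20% | −0.02 | 0.62 | 1.06 | 9% |
| 60% / 30% | 0.00 | 0.62 | 0.74 | 13% |

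In every proportional row the rejection rate is 4% to 5%, which is no more than alpha.

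**A larger effect does not rescue the model.** With a true effect of 1.5 SD and attendance 80% / 15%, power falls from 82% to 5% (proportional) or from 85% to 16% (unrelated).

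The low starting power comes from the sample size and is a separate matter: 10 per group at a difference of 0.65 SD gives 28% by the two-sample t test.

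**The case against.** The strongest reply is that the damage depends on how controls are coded, which the protocol does not say and a statistical analysis plan might. Giving controls the exercise-arm mean, or centring attendance within arm, leaves the estimate at about 0.65 with SE about 0.45. That is correct, but it assigns attendance to children who had nothing to attend, and it works only by making the covariate irrelevant to the contrast with control. It is a reason to leave attendance out.

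Second, the fall to zero needs benefit proportional to attendance. If benefit rises up to 50% attendance and then levels off, the zero-coded estimate at 80% / 15% is about 0.62, with almost no bias and SE about 1.47. At 60% / 30% it is about 0.26, against about 0.55 without attendance. Attendance may also be confounded with motivation or symptoms. This stands: the bias ranges from slight to complete, and where it is slight at 80% / 15% the loss of precision remains.

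Third, some side points are weaker. Adherence is listed among the secondary outcomes to which the model applies, so attendance is on paper both outcome and covariate. But it has no T0 value and hence no change score, so this is probably loose drafting. Baseline measurement may be intended for ADHD symptoms and sports skill, and the time label is a detail often left to a later plan. Attendance has no baseline reading, so the main point does not depend on these.

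**Conclusion.** The concern holds. The only stated model for the primary outcome includes a post-randomisation variable that is zero or missing for an entire arm, and nothing else in the protocol repairs this. That structural fault needs no numerical assumption.

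The size depends on coding and on attendance. With controls missing, the main hypothesis cannot be tested. With controls coded zero and 10 per arm, the estimated effect falls to about 0 if benefit is proportional to attendance. If benefit is unrelated to attendance, the SE is about 1.5 to 5.8 times larger across the assumed attendance range, and power drops from about 25% to between 5% and 13%. Because this is the primary analysis, it must be corrected before the data are analysed.

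**What to change.** 1. Remove attendance from the outcome model.
2. Remove sports skill, which has no defined measurement.
3. Keep only covariates fixed before randomisation: age, and ADHD symptoms stated explicitly as the T0 SWAN score.
4. State that all randomised children are analysed in their allocated arm, and that those who stop training are still tested at T1. With attendance gone, this keeps the comparison as randomised.
5. Report attendance descriptively as adherence, and explore its relation to outcome in a separate dose-response analysis within the two exercise arms, labelled as non-randomised.

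The cost is a change of wording under Statistical analyses. It needs no extra children, and it frees two model degrees of freedom, which matters with about 30 evaluable children. Keeping children who stop training in the T1 assessment takes some follow-up effort, but the visit is already planned.
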